### Study procedures

After signing the informed consent form, participants will complete the baseline assessment, comprising standardised questionnaires on sociodemographic factors, health-related quality of life, self-efficacy, motivation for behaviour change and knowledge about risk/protective factors for dementia (see ‘Outcomes and measures’ section). A reminder will be sent per email to those having consented but did not complete the baseline assessment after 2 weeks. If no baseline data are submitted after this reminder, only the signed consent and minimal contact information will be retained for documentation purposes, and no other personal data will be processed. Consenting participants will then be able to download the MyBraincoach-app. All participants will receive a reminder via email 2 weeks after enrolment in the study to encourage download and use of the app.

At the end of the intervention period (12 weeks), all participants will receive an email with a link to the follow-up assessment, containing the same questionnaires as used at baseline, as well as assessing perceived use and usability of the app. During the follow-up assessment, participants can provide consent to be re-contacted for participation in the video-based focus group. A remote focus group with an expected duration of 90–120 min will then be scheduled, including n=8 pilot study participants, moderated by a researcher experienced in qualitative methodology. Participants will be purposively selected from those consenting to be re-contacted. Subject to participant availability, selection will aim to include individuals with different levels of app engagement, varied educational and sex backgrounds.

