### Outcomes and measures

As this pilot study is not designed to assess intervention effectiveness, no single primary endpoint was specified. The primary objective is to assess the feasibility and acceptability of the adapted MyBraincoach app and the associated study procedures. No single primary endpoint was specified, as the study is not designed to assess intervention effectiveness. Key feasibility outcomes include feasibility of recruitment, success rate of retention of participants at 12 weeks follow-up, app use, perceived usefulness and usability of the app, as well as reasons for dropout in participants who will have discontinued participation (assessed via email).

As exploratory outcomes, we will assess knowledge of risk and protective factors for dementia (dementia literacy), change in dementia risk profiles (risk/protective factors exhibited by participants), perceived barriers towards and motivation for behaviour change. Changes in dementia risk profiles are expected primarily in behavioural and symptom-related components of the LIBRA-score, including nutrition, physical activity, alcohol consumption, smoking, cognitive and social activity, sleep and depressive symptoms. Chronic conditions like, for example, diabetes or coronary heart disease are not expected to resolve during the 12-week intervention and will be used primarily to characterise participants’ risk profiles. The same instruments will be administered both at baseline and follow-up to assess changes in the LIBRA-score and its individual components, based on participants’ self-report. A full description of outcomes and respective assessments applied is given in table 1.

**Table 1 T1:** Outcomes and assessments to be used in the course of the pilot study

Construct	Instrument	BL	FU
Key feasibility outcomes			
Success and feasibility of recruitment	Information on: numbers of individuals (1) interested in the study, (2) signed informed consent, (3) eligible for participation; time necessary for recruitment; response to each recruitment channel; diversity of participants; time and resources spent on different recruitment channels; time from initial contact to enrolment, collected at study centre, standardised forms	x	
Retention rate	Rate of participants completing the follow-up assessment		x
App use	Meta-data on (1) downloads of the app, (2) interactions with the app, (3) app modules used, (4) topics chosen to address, (5) number of notifications received		x

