Usability	German mHealth App Usability Questionnaire – Short Version (G-MAUQ^44^)		x
Usefulness	Technology Acceptance Model Questionnaire (TAM^45^)		x
Non-use of the app, dropout	Standardised questions on reasons for non-use of the app or leaving the study in participants who will have dropped out		x
Exploratory outcomes			
Changes in dementia risk profile	LIBRA-score, comprising information on: *Nutrition*: Mediterranean Diet Adherence Screener (MEDAS^46^); Dietary Fat and Free Sugar – Short Questionnaire (DFS^47^) *Physical activity*: International Physical Activity Questionnaire (IPAQ^48^) *Cognitive activity*: ‘Leisure Time’-scale of the Cognitive Reserve Index Questionnaire (CRIq^49^) *Alcohol consumption, smoking*: standardised questionnaire^50^ Hypercholesterolaemia, diabetes, hypertension, obesity, coronary heart disease, chronic kidney disease: standardised questionnaire^51^ *Depression*: Patient Health Questionnaire (PHQ-9^52^) *Social activity*: Lubben Social Network Scale (LSNS-6^53^); loneliness (UCLA Loneliness Scale^54^) *Hearing impairment*: Mini-Audio-Test (MAT^55^); possession and use of hearing aids *Sleep*: Athens Insomnia Scale for non-clinical application (AIS-NCA^56^)	x	x
Dementia literacy	Standardised questionnaire on knowledge of modifiable risk factors for dementia^19 20^	x	x
Health-related quality of life	EuroQol Visual Analogue Scale (EQ-VAS^57^)	x	x
Self-efficacy	General self-efficacy^58^; domain-specific self-efficacy (LIBRA-factors nutrition, physical activity, social activity, cognitive activity, smoking cessation, alcohol consumption^59^)	x	x
Motivation for behaviour change	Standardised questionnaire, as applied in Zülke *et al*^60^; reason for participation (standardised forms)	x	x
Sociodemographics	Standardised questionnaire (age, sex, education, occupational status, living situation, marital status)	x	

BL, baseline; FU, follow-up; LIBRA, LIfestyle for BRAin Health.

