### Data analysis plan

#### Quantitative analyses

All acquired data will be examined for potential inconsistencies and missing values. Drop-out analyses will assess potential systematic biases between participants who complete the follow-up assessment 12 weeks after baseline and non-completers, using χ² and two-sample t-tests, as appropriate. Success and feasibility of recruitment, retention of participants, use and usability of the app as well as reasons for dropouts will be described using means (SDs) and percentages, as appropriate. Changes in LIBRA, dementia literacy, health-related quality of life, self-efficacy and motivation for behaviour change will be described using dependent samples t-tests. The significance level of all analyses will be set to p<0.05 (two-tailed). Analyses will be conducted using Stata/SE V.16.0. Results will be reported according to the extended guidelines of the CONSORT statement for pilot and feasibility trials.^30^

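### Usability and usefulness are rated only at the 12-week follow-up, so the ratings come from follow-up responders and may be too favourable if people leave because of the app

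*Protocol article*

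**What the plan says.** The protocol article (Study procedures) states that, once the intervention ends, "all participants will receive an email with a link to the follow-up assessment, containing the same questionnaires as used at baseline". Ratings of the app are added to this 12-week survey, which the article describes as "as well as assessing perceived use and usability of the app". Table 1 marks the usability questionnaire and the "Technology Acceptance Model Questionnaire (TAM") once each, in the follow-up column. No rating is scheduled earlier or at the time of leaving.

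Outcomes and measures lists perceived usefulness and usability among the key feasibility outcomes, next to "reasons for dropout in participants who will have discontinued participation (assessed via email"). For dropouts, Table 1 plans standardised questions on why they did not use the app or left the study. It does not plan either rating scale for them.

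Under Quantitative analyses, "use and usability of the app as well as reasons for dropouts will be described using means (SDs) and percentages". The same section compares people who complete the follow-up with those who do not. Sample size expects 60 of 75 participants to provide follow-up data.

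**The concern.** For most outcomes, dropout may or may not relate to the missing value. Here the link is direct: someone who finds the app difficult or of no use has a reason to leave, and then gives no rating. A summary of those who answered would then describe the more satisfied part of the users.

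The ratings are part of the feasibility evidence that is meant to inform refinement of the app and the decision on a confirmatory randomised trial. The people who struggled are also the most informative source for refinement. The focus group does not fill the gap, because consent to be re-contacted for it is given during the follow-up assessment, so it too draws on follow-up responders.

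This is a matter of what is collected and when. No later analysis can recover a rating that was never requested.

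**Working it through.** **Inputs**
- 75 enrolled, 60 with follow-up data, 20% dropout: Sample size.
- 69.2% of users considered the app useful: Dutch primary care study, cited in the Introduction. It serves here only as an illustrative value for raters, p.
- Share of app users without a rating, d: assumed 20%. The plan's 20% refers to enrolled participants, so the share among users may differ.
- Share of unrated users who would call the app useful, q: not in the documents, so it is varied.

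**Step 1: the plan's own figure.** 60 / (1 − 0.20) = 75, which reproduces the stated enrolment. Hence 75 − 60 = 15 participants are expected to have no G-MAUQ or TAM rating.

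**Step 2: formula.** Value for all users = (1 − d) × p + d × q. Overstatement = p minus that value = d × (p − q).

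**Step 3: percentage rating the app useful, with p = 69.2% and d = 0.20.**

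| q (assumed) | All users | Overstatement |
|---|---|---|
| 0% | 0.8 × 69.2 + 0.2 × 0 = 55.4% | 13.8 points |
| 25% | 0.8 × 69.2 + 0.2 × 25 = 60.4% | 8.8 points |
| 50% | 0.8 × 69.2 + 0.2 × 50 = 65.4% | 3.8 points |
| 69.2% | 69.2% | 0 points |

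**Step 4: mean scores.** The overstatement is d × (mean of raters − mean of leavers). With d = 0.20, gaps of 0, 0.25, 0.5 and 1.0 SD give 0, 0.05, 0.10 and 0.20 SD.

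**Step 5: dependence on d.** The worst case (q = 0) equals d × 69.2%. For d = 0.10 it is 6.9 points, for d = 0.20 it is 13.8 and for d = 0.30 it is 20.8. If many dropouts never opened the app, the share of users without a rating is below the dropout rate and the possible bias shrinks.

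**Step 6: comparison with sampling error.** With 60 raters, the 95% half-width around 69.2% is 1.96 × √(0.692 × 0.308 / 60) = 11.7 points. The intermediate cases lie inside that width and the worst case lies outside it. A confidence interval computed from the raters does not reflect this bias at all.

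**Step 7: what the other planned data give.**
- Exit reasons can indicate that the app drove someone away, but they are not G-MAUQ or TAM scores and depend on a reply.
- App metadata show engagement, not perceived usability.
- The completer comparison cannot be made on the ratings, because non-completers have none.

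**The case against.** The strongest counter-argument is that stopping the app is not the same as leaving the study. Every participant is sent the follow-up link, so someone who gives up on the app in week 4 can still rate it in week 12. Only those who withdraw or ignore the survey are lost, and those who left because of the app are a subset of unknown size. This stands, and it limits the point.

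Second, the plan already measures part of the mechanism. Reasons for non-use and dropout are collected, and problems can be documented within the app. Metadata are linked to the questionnaires by study ID, and the completer comparison is not restricted to baseline variables, so engagement can be compared too. This also stands, although none of it yields a rating.

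Third, no usability or usefulness threshold is stated that a few points could cross, and retention is reported, so a reader can see how many did not answer. That lowers the stakes but leaves the selection in place.

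Fourth, leavers may not answer a second form either, and a rating after four weeks is not equivalent to one after twelve. Both are fair limits on the remedy. They argue for showing the two groups of ratings separately, not against asking.

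**Conclusion.** The point holds in a limited form. The ratings for two key feasibility outcomes will come from follow-up responders only, about 60 of 75 by the plan's expectation. They may be too favourable if dissatisfaction with the app is a cause of leaving.

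A reader might infer that the ratings are bound to be too favourable, or that a particular excess of several points can be expected. The documents do not support either. They give no evidence on why participants will leave or how leavers would rate the app, and bias is zero if leavers would rate it as responders do.

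The range of 0 to 13.8 points rests on two assumptions: 69.2% useful among raters, taken from a study of different design, and 20% of app users unrated. The Dutch community study reported only 56% app use, which shows that enrolled participants and app users can be quite different denominators.

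This is an inexpensive improvement to data collection, not an error that undermines the study.

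**What to change.** In the dropout email already planned, add the G-MAUQ short version and the TAM usefulness items as optional items after the questions on reasons, for anyone with at least one app login. Offer the same short form, on its own, to people who do not respond to the 12-week survey.

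In the report:
- give the number of raters among app users;
- show early-leaver ratings separately from the 12-week ratings, not only pooled;
- add a worst-case bound that counts unrated users as unfavourable;
- read the ratings together with the dropout reasons and usage data.

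The cost is one extra short online form and a few descriptive lines. Response from leavers will be incomplete, their ratings will follow differing lengths of exposure, and the bound will look less favourable than the responders' figure. Recruitment is planned to start on 1 November 2026, and the form should be in place by then.

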Against this background, we aim to test a translated and adapted version of an evidence-based mHealth intervention for dementia risk reduction, the MyBraincoach-app,^29^ in a pre-post pilot study among German adults aged 40–75 years. Feasibility and acceptability will be evaluated in terms of:

Feasibility of recruitment.Success rate of retention of participants at 12 weeks follow-up assessment.Usage (patterns) of the app.Perceived use and usability of the app.Reasons for non-use and study dropout.

Further exploratory objectives are:

To investigate change in knowledge of risk and protective factors for dementia.To describe changes in dementia risk profiles at 12 weeks follow-up.To assess changes in self-efficacy, motivation for behaviour change and health-related quality of life.To gain exploratory insights into participants’ perception of the app by means of a moderated focus group.

A proof-of-concept-study in community-dwelling middle-aged adults in the Netherlands investigated usage patterns and appreciation of the Dutch app (V.1.0), as well as changes in knowledge and attitudes towards dementia risk reduction.^29^ While overall app use was modest (56%), those who used the app evaluated it positively, increased their knowledge on dementia risk reduction and showed more positive beliefs about health behaviour change at follow-up. In a further proof-of-concept-study testing the app in Dutch primary care patients (n=188), 69.2% of users considered the app useful.^28^ The app improved knowledge on dementia risk reduction, while dementia risk improved in both the intervention (GP consultation+app) and control group (GP consultation only).

The present study aims to provide context-specific evidence on recruitment and retention, patterns of app engagement, perceived usefulness and usability and accessibility of an adapted version of the app in a German setting. By combining a quantitative feasibility assessment with qualitative user feedback, it will provide implementation knowledge required to refine the intervention and inform the design of a subsequent RCT.

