### Sample size

As our study is a pilot study applying a pre-post design, a power analysis to determine sample size was not indicated. To assess use and usefulness of the MyBraincoach app, a sample size of n=75 is deemed sufficient to obtain data of n=60 participants for analyses at follow-up, expecting a dropout rate of 20%.

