#### Qualitative analyses

A single remote, video-based focus group targeting n=8 participants will be conducted as a formative supplement to the quantitative feasibility assessment. The focus group is intended to provide exploratory insights into app use and usability and identify suggestions for intervention refinement, rather than to achieve thematic saturation. A researcher experienced in group interviews will moderate the focus group (expected duration: 90–120 min), which will be conducted using appropriate software (eg, Zoom). The interview guide will be designed following the guidelines for problem-centred interviews,^42^ a semi-structured type of interview aiming to provide impulses for discussion and free narration of participants. Topics to be covered include previous experience with eHealth/mHealth tools, previous knowledge of lifestyle factors relevant for dementia risk reduction, perception of app-design, use and usability of specific app-features, evaluation of app content and suggestions for improvement, using open-ended questions. The focus group will be video-recorded and transcribed fully by an experienced transcribing service.

Content of the focus group will be analysed using structured content analyses.^43^ First, categories will be built inductively to analyse interview transcripts (coding scheme). Second, transcripts and derived categories will be entered into MAXQDA software. Finally, blocks of transcripts will be assigned to the coding scheme. Results will be processed quantitatively in MAXQDA. Sociodemographic information of focus group participants (age, sex, education) will be analysed descriptively using Stata.

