### Consent to participate

All participants in the pilot study will provide online informed consent to participate prior to participation, using an electronic Transport Layer Security-encrypted consent form. Potential participants will be informed about details of the study, voluntariness of participation, the option of discontinuing participation at any time and details on data protection. Usability testers will sign a written informed consent form prior to the usability testing session. Participants having agreed to be re-contacted after the pilot study and willing to participate in the focus group will sign an additional online informed consent prior to participation in the focus group.

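### Re-contact consent for the focus group is asked for only in the 12-week follow-up, so participants who do not return cannot be selected and the intended range of app engagement is cut short at one end

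*Protocol article*

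**What the plan says.** The Study procedures section of the protocol article sets both the timing and the sampling frame of the focus group. On timing: "During the follow-up assessment, participants can provide consent to be re-contacted for participation in the video-based focus group". On the frame: "Participants will be purposively selected from those consenting to be re-contacted". On the purpose of the selection, subject to who is available: "selection will aim to include individuals with different levels of app engagement, varied educational and sex backgrounds".

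The Consent to participate section adds a second step but no second route: "Participants having agreed to be re-contacted after the pilot study and willing to participate in the focus group will sign an additional online informed consent".

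Table 1 (Outcomes and measures) defines retention as "Rate of participants completing the follow-up assessment". The questionnaire that carries the re-contact question is thus the one that decides whether a person counts as retained.

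The Sample size section states that "a sample size of n=75 is deemed sufficient to obtain data of n=60 participants for analyses at follow-up, expecting a dropout rate of 20" per cent. The Qualitative analyses section describes the component: "A single remote, video-based focus group targeting n=8 participants will be conducted as a formative supplement to the quantitative feasibility assessment".

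Two further provisions bear on the point. The follow-up link is emailed to all participants, whether or not they used the app. Reasons for dropout are asked by email, and Table 1 lists standardised questions on non-use and on leaving the study.

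**The concern.** A purposive sample can only be as varied as the frame it is drawn from. Here the frame consists of people who came back at 12 weeks and agreed to be contacted. Those who left the study are never asked, so their absence comes from the procedure and not from their own refusal.

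This works against the wish to include people with different levels of engagement, because some of those who stopped using the app are likely to be among those who stopped taking part. The focus group is also one of the sources meant to guide changes to the app before the planned randomised trial. A group made up only of follow-up respondents may say less about the barriers that lead people to stop. Standardised questions by email record reasons for leaving, but they do not replace the open discussion planned for the group.

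No feasibility estimate, sample size or quantitative analysis is at stake.

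**Working it through.** **Step 1: is there any other route into the group?** I compared the sections that mention the focus group.

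- Study procedures: re-contact consent during the follow-up assessment; members selected from those who gave it.
- Consent to participate: additional consent, limited to people who already agreed to re-contact.
- Study design, Qualitative analyses, and Patient and public involvement: size, purpose, content and timing of the group; no other invitation.
- Outcomes and measures: dropouts are emailed about their reasons; no offer of the focus group is mentioned.

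The word 'only' is my reading. It follows from one stated consent point combined with a frame restricted to those who used it.

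**Step 2: reproduce the plan's sample size.** Inputs from the Sample size section: 60 wanted at follow-up, 20% dropout.

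60 / (1 − 0.20) = 75, which matches the stated figure.

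**Step 3: number who cannot be selected.**

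75 × 0.20 = 15 expected dropouts, leaving a frame of at most 75 − 15 = 60, and fewer if some completers decline re-contact. One marginal exception: a person who opens the follow-up, agrees to re-contact and then stops would count as not retained but could still be reached.

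**Step 4: share of non-users out of reach.** The protocol gives no expected share of non-users for this study. As an assumption only, take the complement of the 56% app use that the Introduction reports for an earlier Dutch study: 44%. The article does not define that 56%, so reading the remainder as people who never used the app is itself an assumption.

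- Non-users: 75 × 0.44 = 33.
- Dropout unrelated to use: 0.20 × 33 = 6.6, that is 20% of non-users. This percentage does not depend on the 44%.
- All 15 dropouts are non-users (the extreme case): 15 / 33 = 45%. Even then 33 − 15 = 18 non-users remain among the 60 completers, before anyone declines.

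**Step 5: what a wider frame could add.** If all 75 could be approached and all would accept, a random draw of 8 would contain on average 8 × 15 / 75 = 1.6 dropouts. The probability of at least one is

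1 − C(60,8) / C(75,8) = 0.85.

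For assumed dropout of 10% (8 people after rounding) to 30% (22 people), the same formula gives 0.61 to 0.95. Under the stated procedure the corresponding probability is 0, apart from the exception in Step 3. The figures for the wider frame are upper bounds, because dropouts are less certain to accept an invitation, and the actual selection is purposive, not random.

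**The case against.** The strongest reply is that engagement with the app is not the same as retention in the study. Every participant receives the follow-up link, so people who used the app little or not at all can answer it, agree to re-contact and be chosen. Even in the extreme case above, 18 non-users would be left for a group of 8. The engagement aim is also worded as an aim and made subject to availability. This stands: a reader might infer that the procedure contradicts the aim, but the documents support only that it narrows what the aim can achieve.

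A reader might also infer a conflict with the feasibility objective "Reasons for non-use and study dropout". The documents do not support that. This objective has its own instruments, namely the email enquiry and the standardised questions in Table 1, and the app metadata add information on use. The focus group serves a separate exploratory objective about how participants perceive the app. Dropouts are missing from the group, not from the study's feedback as a whole.

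Third, the discussion topics (design, features, content, improvements) largely presuppose some exposure to the app, and the group is a formative supplement that does not seek saturation. This lowers the weight of the point and argues against reserving places for non-users. It does not remove the point. Someone who used the app for some weeks and then left has relevant experience, and with a single group of eight it matters who can be invited. The availability clause covers people who are asked and cannot come, not people who are never asked.

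**Conclusion.** The point holds in a limited form. As described, participants who do not open the 12-week follow-up cannot enter the focus group. At the planned 20% dropout that is about 15 of 75, and this figure is itself the plan's expectation. The effect is to truncate the range of engagement from which the eight are chosen, not to remove it.

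The share of non-users out of reach is about 20% if dropout is unrelated to use. The 45% figure is tempting but should not be quoted as an estimate. It needs an undefined percentage from a Dutch study to carry over to this sample, and it needs every dropout to be a non-user. The article gives no data on how dropout relates to app use.

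A reader might also infer that the qualitative findings will be biased in a known direction. A tilt towards retained participants is plausible, but the documents give no basis for its size.

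The consequence is moderate and confined to the qualitative component. The change is still worth making because it removes an avoidable selection on retention at almost no cost, provided it is made before enrolment begins.

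**What to change.** Add an optional re-contact box for the focus group to the online consent form at enrolment, where contact details are already collected, and keep the question in the follow-up as confirmation. Then use the app metadata, which the Recruitment section already links to questionnaire data through the study ID, to include people with low use or without a completed follow-up, where they are available, willing and have not withdrawn consent. No fixed quota is needed: with eight places, reserving some would take them from people who can comment on features in use. The separate consent before the focus group stays as it is.

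The cost is one line on the consent form and an ethics notification before the planned recruitment start on 1 November 2026. Once people have enrolled without the box, the gap is harder to close. The downside is that some low-engagement invitees will decline, so the gain will be smaller than the upper bounds above. If the form is left unchanged, the report should at least state that the focus group was drawn from follow-up respondents only.
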